### Randomisation and allocation concealment

#### Sequence generation

Eligible participants will be randomly assigned in a 1:1 ratio to receive either culturally adapted CCT^19^ or ERT.^32^ The randomisation sequence will be generated by an independent statistician using permuted block randomisation with varying block sizes of four, six and eight to minimise predictability. Randomisation will be stratified by study site (LASUTH, FNPHY, NPHA) and by age group (18–21, 22–26 and 27–30 years) to ensure balance across key contextual and developmental variables.

#### Allocation concealment

Allocation concealment will be maintained using sequentially numbered, opaque, sealed envelopes prepared centrally by the independent statistician. Envelopes will be stored securely at each site and opened only after completion of baseline assessments and reconfirmation of eligibility. Site-based research administrators, who are not involved in recruitment or outcome assessment, will oversee envelope opening. Recruiting staff and outcome assessors will have no access to the randomisation sequence.

#### Blinding

The trial employs an assessor-blinded design. Given the nature of the interventions, blinding of participants and facilitators is not feasible. However, all research assistants responsible for outcome assessments at 3, 6 and 12 months will remain strictly blinded to treatment allocation throughout the study period. Several procedures are in place to maintain blinding. Outcome assessors will not be involved in intervention delivery, supervision or fidelity monitoring. Assessments will be conducted in locations physically separate from intervention rooms where possible, and participants will be reminded at each assessment visit not to disclose their group allocation. To evaluate the success of blinding, assessors will be asked to guess each participant’s allocation at the 12-month assessment, and the proportion of correct guesses will be reported. Any instances of accidental unblinding will be documented and reviewed by the Data Monitoring Committee. To minimise contamination between trial arms, facilitators will be assigned exclusively to a single intervention condition, and sessions for different arms will be scheduled on separate days or times where feasible. Control arm facilitators will receive explicit instruction to avoid introducing cognitive strategies or techniques associated with the CCT curriculum.

### Interventions: culturally adapted CCT

#### Theoretical rationale

CCT, originally developed by Twamley *et al*,^19^ is grounded in a compensatory or ‘prosthetic’ model of cognitive rehabilitation. Rather than attempting to remediate underlying neurocognitive deficits through repetitive drill-based exercises, CCT focuses on teaching practical strategies that allow individuals to bypass or offset cognitive limitations in everyday functioning. This approach aligns with evidence suggesting that, in psychosis, cognitive impairments are relatively stable over time and only modestly responsive to pharmacological or restorative interventions.

CCT targets the translation of cognitive skills into real-world contexts by emphasising habit formation, environmental modification and strategic problem-solving. By prioritising functional relevance over cognitive performance per se, the intervention seeks to enhance autonomy, role functioning and participation in daily activities. This emphasis is particularly salient in early psychosis, where timely support for functional recovery may alter longer-term trajectories.

From an implementation perspective, CCT is well suited to low-resource settings. Its manualised structure and adaptability to group formats render it amenable to task-shifted delivery by non-specialist health workers, provided that adequate training and supervision structures are in place.

#### Cultural adaptation process

The CCT curriculum underwent a systematic cultural adaptation process using YPAR principles. Young people with lived experience of psychosis were engaged as co-designers throughout the adaptation phase, contributing to decisions regarding language, examples, delivery style and perceived relevance of cognitive strategies. This participatory approach was intended to enhance cultural resonance, acceptability and sustained engagement. Key adaptations included translation of materials into simplified English and Nigerian Pidgin English, with careful attention to maintaining conceptual clarity rather than literal equivalence. Western-centric examples embedded in the original curriculum were replaced with locally salient scenarios reflecting the everyday cognitive demands faced by young Nigerians, such as navigating public transportation (eg, *danfo* buses), managing informal employment or market trading, adhering to medication schedules within extended family households, and balancing religious or community obligations.

#### Intervention structure and delivery

The adapted CCT intervention consists of 12 weekly group sessions, each lasting between 60 and 90 min. A detailed overview of the curriculum content is provided in online supplemental file 1. Sessions are delivered to groups of six to eight participants to balance opportunities for peer interaction with individualised support. All sessions are conducted in designated group therapy rooms within participating hospitals, embedding the intervention within routine service settings.

Each session follows a standardised structure to promote consistency and skill consolidation. Sessions begin with a brief welcome and review of the session agenda, followed by discussion of homework assignments from the previous week. Core content is introduced through brief didactic teaching and live demonstrations, after which participants engage in guided practice exercises, including role-plays and problem-solving activities tailored to their own daily challenges. Sessions conclude with the collaborative assignment of personalised homework tasks designed to encourage real-world application of strategies.

Participants receive a printed workbook containing session summaries, worksheets and practical exercises, as well as wallet-sized cue cards highlighting key strategies.

#### Curriculum content

The curriculum targets four core neuropsychological domains commonly impaired in FEP:

**Prospective memory and organisation (sessions 1–2):** These introductory sessions establish a foundation of external support to alleviate the cognitive load on memory systems. Session 1: Focuses on using calendars to maintain long-term organisation and scheduling. Session 2: Introduces reminders and environmental cues to ensure tasks are completed at the appropriate time, addressing the ‘Remembering to remember’ aspect of prospective memory.**Attention and working memory (sessions 3–5):** This domain transitions from external tools to the active management of information while it is being processed. Session 3: Targets short-term memory capacity, specifically the ability to retain information while simultaneously performing other actions. Session 4: Cultivates ‘Conversational Attention,’ emphasising the importance of listening well during interpersonal exchanges. Session 5: Prioritises ‘Task Attention,’ helping participants sustain focus on specific objectives to avoid distractions.**Verbal learning and memory (sessions 6–8):** These modules move into the encoding and retrieval of information, leveraging specific mnemonic and organisational strategies. Session 6: Establishes the groundwork for learning new verbal information. Session 7: Teaches categorisation or ‘grouping,’ a strategic encoding technique where related items are clustered to improve recall efficiency. Session 8: Focuses on delayed memory, ensuring that information encoded previously can be successfully retrieved after a period of time.**Executive function: flexibility, problem-solving and planning (sessions 9–12):** The final phase of the programme addresses higher-order cognitive control and the integration of previously learnt skills. Sessions 9 and 10: Develop cognitive flexibility, encouraging participants to ‘Think in New Ways’ and formulate a ‘Plan B’ when initial strategies fail. Session 11: Emphasises the pre-emptive phase of tasks, specifically the ability to plan a sequence of actions before execution. Session 12: Functions as a synthetic review where all compensatory skills are integrated and the programme concludes with a celebration of the mastered strategies.

Across all modules, facilitators explicitly link cognitive strategies to participants’ personally meaningful goals, reinforcing relevance and motivation. A full description of the intervention according to the Template for Intervention Description and Replication (TIDieR) checklist is available in facilitators, training and supervision: In line with the task-shifting model, CCT sessions are facilitated by psychiatric social workers rather than specialist neuropsychologists. These facilitators are already embedded within routine mental health services and possess experience in group-based psychosocial interventions.

All facilitators complete a 5-day intensive training programme prior to study commencement. Training covers the neurocognitive profile of psychosis, principles of compensatory rehabilitation, group facilitation skills and detailed familiarisation with the CCT manual. Competency is assessed through structured role-play exercises, with facilitators required to achieve at least 90% on standardised competency ratings before delivering intervention sessions.

Ongoing supervision is provided weekly by a senior clinical psychologist or psychiatrist with expertise in psychosis. Supervision sessions focus on reviewing session progress, troubleshooting challenges, reinforcing adherence to the manual and managing clinical risks. To monitor fidelity, a random 20% sample of audio-recorded sessions is independently coded using a study-specific fidelity checklist assessing both content adherence and delivery competence (see online supplemental file 2).

online supplemental file 2

### Control intervention: ERT

#### Rationale and design

The control condition employs an active control design to account for non-specific therapeutic factors such as group contact, facilitator attention, structured routine, transportation reimbursement and positive expectancy effects. This approach strengthens internal validity by allowing observed differences in outcomes to be more confidently attributed to the specific acquisition of compensatory cognitive strategies rather than to general therapeutic engagement. ERT^32^ was selected as an appropriate comparator because it provides meaningful, culturally relevant group activities without directly targeting cognitive processes or teaching structured cognitive strategies.

#### Structural equivalence

To ensure comparability, ERT is matched to the CCT intervention on key structural parameters. Participants attend 12 weekly group sessions of 60–90 min duration, delivered in groups of six to eight participants within the same hospital facilities. Sessions are scheduled with similar frequency and duration, and participants receive identical transportation reimbursement and refreshments. Sessions are facilitated by health educators or psychiatric social workers who are not involved in delivering CCT. Facilitators receive orientation to the control protocol to ensure consistency and to prevent inadvertent introduction of cognitive techniques.

#### Content and boundaries

ERT sessions focus on structured leisure and social activities designed to be enjoyable, engaging and culturally resonant. Activities include creative arts, music and cultural discussions, light physical recreation and facilitated group conversations centred on general well-being and social connection.

To preserve the conceptual distinction between trial arms, the protocol explicitly prohibits the introduction of cognitive strategies, formal problem-solving frameworks, planning techniques or memory aids. Structured homework assignments are not given. Fidelity monitoring procedures are in place to ensure that control sessions do not drift toward therapeutic content that overlaps with CCT.

#### Integrity and contamination safeguards

Several measures are implemented to minimise contamination between intervention arms. Facilitators are assigned exclusively to a single condition and do not cross-deliver sessions. Where feasible, sessions for different arms are scheduled on separate days or times. Supervision structures are kept distinct, and facilitators are regularly reminded of the importance of maintaining protocol boundaries.

### Outcome measures and assessment schedule

#### Assessment schedule

Outcome assessments are conducted at four time points by trained research assistants who remain blinded to treatment allocation throughout the study. Baseline assessments (T0) occur within 2 weeks prior to randomisation. Post-intervention assessments are conducted at 3 months following randomisation (T1; ±2 weeks), corresponding to completion of the 12-session intervention period. Further follow-up assessments are conducted at 6 months (T2; ±2 weeks) and at twelve months (T3; ±4 weeks), the latter constituting the primary endpoint for longitudinal outcomes. The schedule of enrolment, interventions and assessments throughout the study period is detailed in table 1.

This extended follow-up period is intended to capture not only immediate post-intervention effects but also the durability of cognitive and functional changes over time, an issue of particular relevance for early psychosis interventions.

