#### Primary objectives: feasibility and acceptability

**Objective 1 (Feasibility):** To assess the feasibility of recruiting and retaining young adults with FEP into a longitudinal cognitive intervention trial across three public psychiatric hospitals. It is anticipated that recruitment of 180 participants within a 9-month enrolment period will be achievable, corresponding to the recruitment of at least 60% of eligible individuals screened. Retention of at least 70% of randomised participants at the 12-month follow-up is expected. Among participants allocated to CCT,^19^ it is anticipated that at least 75% will attend a minimum therapeutic dose, defined as nine or more of the twelve sessions.**Objective 2 (Acceptability):** To evaluate the acceptability of the culturally adapted CCT intervention among service users and facilitating staff. Acceptability will be operationalised through participant satisfaction scores, with the expectation that mean scores on the Client Satisfaction Questionnaire-8 (CSQ-8)^31^ will reach or exceed 24 out of a possible 32 at the 3-month assessment.**Objective 3 (Fidelity):** To determine whether CCT can be delivered with adequate fidelity and competence by non-specialist health workers within a task-shifted model. It is anticipated that trained psychiatric social workers will achieve at least 80% adherence to manualised content and delivery competence benchmarks, based on independent coding of a sample of audio-recorded sessions.

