#### Study setting

The study will be conducted across three major tertiary public psychiatric hospitals located in Lagos and Ogun States in South-West Nigeria. These facilities were purposively selected on the basis of their high patient volumes, established outpatient services for psychotic disorders, and existing research infrastructure capable of supporting longitudinal clinical trials. Each site also employs psychiatric social workers who are embedded within routine care teams, making them suitable candidates for task-shifted delivery of the intervention.

The participating sites are:

**Lagos State University Teaching Hospital (LASUTH), Ikeja**, a large general teaching hospital with a dedicated psychiatry department providing outpatient and inpatient mental health services.**Federal Neuro-Psychiatric Hospital, Yaba (FNPHY**), one of the busiest specialist psychiatric facilities in Nigeria, managing a high volume of individuals with psychotic disorders annually.**Neuropsychiatric Hospital Aro (NPHA), Abeokuta**, a specialist psychiatric hospital and designated WHO Collaborating Centre with longstanding involvement in mental health research and training.

Recruitment will take place primarily through outpatient clinics and early psychosis service streams within these hospitals. All intervention sessions will be delivered in existing group therapy rooms at the participating sites, ensuring that the study remains embedded within routine service environments and enhancing the ecological validity of findings.

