### Recruitment strategy

Participant recruitment is planned over a 9-month period, from 1 February 2026 to 30 November 2026, using a consecutive sampling approach. This strategy is intended to minimise selection bias while ensuring that the recruited sample reflects the clinical diversity of young people with FEP attending public psychiatric services.

Multiple, complementary recruitment pathways will be employed. Treating psychiatrists, nurses and psychiatric social workers will identify potentially eligible patients during routine outpatient visits and provide brief verbal information about the study. In addition, trained Youth Research Assistants (YRA) who are young people with lived experience of psychosis and have received training in research ethics and engagement will support recruitment by making initial approaches using culturally adapted information sheets available in English and Nigerian Pidgin English.

Eligibility screening will occur in two stages. First, diagnostic eligibility will be confirmed using the MINI V.7.0. Second, cognitive eligibility will be assessed using the BACS. Individuals who meet all eligibility criteria will be invited to provide informed consent prior to baseline assessment.

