### Sample size and pilot rationale

The target sample size is 180 participants, with 90 allocated to each trial arm. In keeping with established guidance for pilot and feasibility trials, the sample size has been selected to provide adequate precision around key feasibility parameters rather than to ensure statistical power for hypothesis testing of clinical outcomes.

Assuming a conservative retention rate of 70%–75% at the 12-month follow-up, a sample of 180 participants allows estimation of retention with a 95% CI width of approximately ±7%. This level of precision is sufficient to apply prespecified ‘traffic light’ progression criteria to inform decisions regarding advancement to a definitive trial.

Although the study is not powered for definitive efficacy analyses, the planned sample size is expected to be sufficient to detect preliminary clinical signals. With 90 participants per arm, allowing for attrition, the study retains approximately 80% power at a two-sided alpha level of 0.05 to detect a medium effect size (Cohen’s d=0.50) on the BACS composite score. This calculation accounts for clustering effects associated with group-based intervention delivery, assuming an intraclass correlation coefficient (ICC) of 0.05.

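### The 3-month visit is equated with the end of the 12-session course, but the plan allows no time for therapy groups to fill

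*Protocol article*

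**What the plan says.** Under Assessment schedule, the T1 visit has a fixed clock and a stated meaning: "Post-intervention assessments are conducted at 3 months following randomisation (T1; ±2 weeks), corresponding to completion of the 12-session intervention period". The same section limits the gap before randomisation: "Baseline assessments (T0) occur within 2 weeks prior to randomisation".

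Allocation is individual: "Eligible participants will be randomly assigned in a 1:1 ratio". Under Allocation concealment, the envelope is opened once baseline is complete and eligibility has been reconfirmed.

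Delivery is in groups. For CCT, "Sessions are delivered to groups of six to eight participants"; Structural equivalence gives the same size for ERT. The CCT curriculum runs in order, from introductory sessions to a closing review, and each session discusses the previous week's homework.

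Recruitment is planned so that "recruitment of 180 participants within a 9-month enrolment period will be achievable", at three hospitals (Study setting). Recruitment strategy adds: "Participant recruitment is planned over a 9-month period, from 1 February 2026 to 30 November 2026, using a consecutive sampling approach".

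The CSQ-8 is a primary outcome measured only at 3 months. Table 3 makes a mean of at least 24 the green threshold, and Analysis of primary outcomes compares the lower confidence bound with the criteria.

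**The concern.** T1 can coincide with the end of a 12-week course only if the course starts soon after randomisation. With consecutive recruitment and individual envelope opening, a participant randomised early in the formation of a group must wait until enough others have been allocated to the same arm at the same site. The plan makes no allowance for that wait, yet it states the equivalence as a fact.

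If the wait is long, the single CSQ-8 measurement mixes ratings of a complete course with ratings of a partial one, and exposure depends on the order of arrival. The mean that feeds the progression decision would then not be purely a post-intervention rating. The 3-month BACS and UPSA-N values, meant in part to show immediate effects, would mix exposures in the same way.

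**Working it through.** **Inputs.** 180 participants, 90 per arm (Sample size and pilot rationale); 9 months (Objective 1, Recruitment strategy); three sites (Study setting); groups of 6 to 8 and 12 weekly sessions in both arms; T1 at 3 months ±2 weeks. One month is 365.25/12/7 = 4.348 weeks.

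**The stated equivalence.** Session 12 falls 11 weeks after session 1. Three months is 13.04 weeks, so the window runs from 11.04 to 15.04 weeks. T1 on its target date follows session 12 if session 1 falls within 13.04 − 11 = 2.04 weeks of randomisation. On the last permitted day it does so if session 1 falls within 15.04 − 11 = 4.04 weeks. The equivalence is therefore correct for a prompt start only.

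**Accrual.** 180/9 = 20 per month; 20/3 = 6.67 per site; 6.67/2 = 3.33 per site and arm. The spacing between members of the same group is 4.348/3.33 = 1.304 weeks.

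**Waiting, with closed groups that start when full.** Member k of n waits (n − k) × 1.304 weeks. Three spacings (3.9 weeks) fit within 4.04 weeks and four (5.2 weeks) do not, so the first n − 4 members are unfinished when the window closes. Two spacings (2.6 weeks) exceed 2.04, so the first n − 2 are unfinished on the target date.

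| Group size | First member waits (weeks) | Not yet offered session 12 at target date | Not yet offered session 12 at window close |
|---|---|---|---|
| 6 | 5 × 1.304 = 6.5 | 4/6 = 67% | 2/6 = 33% |
| 7 | 6 × 1.304 = 7.8 | 5/7 = 71% | 3/7 = 43% |
| 8 | 7 × 1.304 = 9.1 | 6/8 = 75% | 4/8 = 50% |

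**Random arrivals.** A simulation with random arrival times and permuted blocks of 4, 6 and 8 stratified by site and age gave 34% (n = 6) to 50% (n = 8) at window close, and 58% to 69% at the target date.

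**Sensitivity at window close, n = 6 to 8.**
- Site with half of all accrual: 5.0 per arm per month, spacing 0.87 weeks, first n − 5 members unfinished: 1/6 to 3/8 = 17–38%.
- Site with a quarter of accrual: 2.5 per arm per month, spacing 1.74 weeks, first n − 3 unfinished: 3/6 to 5/8 = 50–62.5%.
- The calendar dates in Recruitment strategy span 10 months, not 9. At that rate (3.0 per site and arm per month) the simulation gave 39–54%.
- Rolling entry: the wait is at most about 1 week, session 12 falls by about week 12, and the share is near zero.

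**Batching.** One group per arm needs 12 to 16 participants at a site, which takes 12/6.67 = 1.8 to 16/6.67 = 2.4 months. In the 2 weeks allowed between baseline and randomisation a site accrues (6.67/4.348) × 2 = 3.1. A batch can therefore meet the 2-week rule only if baselines are deliberately held back until the batch is assembled.

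**The case against.** The strongest objection is that the document never says groups are closed. For CCT the ordered curriculum, homework review and closing session imply it. ERT is leisure activity without structured homework, and nothing comparable points to closed ERT groups. With rolling entry the problem disappears. This stands, and it makes the size conditional. Even accrual across sites and months is also an assumption.

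A second objection is that batching is already possible. No maximum interval is set between screening or consent and baseline, Table 1 separates screening from baseline, and eligibility is reconfirmed before the envelope is opened. A reader might infer that the 2-week baseline rule prevents batching; it does not. But the article describes consecutive recruitment and an envelope opened after each baseline. Followed as written, that makes its own statement about T1 untrue for a sizeable share of participants. This goes beyond operational detail left to a fuller document.

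Three further readings are tempting and not supported:
- That most participants are assessed too early. The 58–69% at the target date ignores the two further weeks that the window allows.
- That adherence is also distorted. Table 1 marks attendance at T1 as well as during the intervention, and 12–24% would have been offered fewer than nine sessions by window close. But the outcome is defined on the 12 sessions with no cut-off date, and Table 2 collects it during the intervention.
- That the CSQ-8 mean is biased in a known direction. Nothing in the document shows the direction or the amount, and progression does not rest on any one criterion.

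**Conclusion.** The concern holds in conditional form. The stated match between T1 and the end of the course needs session 1 within about 2 weeks of randomisation, or 4 weeks at the very latest, and the plan's own accrual and group size do not deliver that. With closed groups and even accrual, about one third to one half of members would not have been offered session 12 when the T1 window closes. The range is 17–38% at a site with half of all accrual, and near zero with rolling entry.

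What is exposed is the CSQ-8 progression criterion and the exploratory 3-month contrasts. The 12-month contrast, which is the main clinical parameter, is little affected: every course would be over, with only the time since completion varying. Retention is judged at 12 months and fidelity from recordings, so T1 timing does not touch them. The passages on recruitment, allocation and assessment timing should be reconciled.

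**What to change.** Keep the randomisation clock and state, under Recruitment strategy, Allocation concealment and Assessment schedule, that:
- participants are screened and consented first;
- baseline is done only in the 2 weeks before a site batch large enough for one group per arm (12 to 16 participants) is randomised;
- both arms' groups start within about 2 weeks of randomisation, so that session 12 falls by about week 13.

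The cost is that some consented patients wait up to about 2 months and may drop out before randomisation. They should be counted in the recruitment rate, whose denominator is already eligible individuals. No extra staff or visits are needed.

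If batching is not used, collect at least the CSQ-8 after the group's last scheduled session, in both arms. Do not move the whole T1 battery while T2 stays fixed. The first member of a group of eight would finish at 9.1 + 11 = 20.1 weeks and could have T1 as late as 22.1 weeks if 2 weeks are allowed. T2 opens at 26.1 − 2 = 24.1 weeks, so BACS and UPSA-N could be repeated about 2 weeks apart.
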